### 2.7. Sample Size

The sample size was calculated based on differences in MD adherence score (primary outcome) measured by MEDAS and KIDMED questionnaires. The sample size was estimated using the analysis of variance (differences between 8 study groups). It was assumed that the alpha value would be equal to 0.05 and beta 0.20, exactly as reported in previous studies [61], with a common standard deviation equal to 1.19. The minimum group size needed to detect a minimum increase of 1 point in the intervention group’s MEDAS compared to the control group is equal to 45 families per study group (15 families per country). The total sample is, therefore, 45 × 8 = 360 families. However, assuming a 25% drop-out rate, the minimum group size is equal to 60 families per study group (20 families per country). Overall, 160 families will thus be recruited per country after obtaining the approval of the Ethics Committee of each recruiting center and written informed consent from parents and adolescents.

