### 2.8. Criteria for Discontinuing or Modifying Allocated Intervention

If a severe or unanticipated adverse event (AE) occurs that may influence the risk/benefit ratio of this study, the principal investigator must report this to the ethics committee and permanently discontinue the family from the intervention. Participating families will be asked to report any AEs experienced during the entire intervention. For each AE, the onset date, intensity, relationship to the study product, action taken, and outcome will be recorded by researchers in accordance with the Medical Dictionary for Regulatory Activities (MedDra dictionary), Version 24.0 of MedDRA (Spanish), March 2021. In case of the suspicion of a major AE, such as an allergic reaction, the case will be referred directly to the study doctor, who will evaluate the symptoms and signs and adopt the necessary measures according to their severity.

In addition, the researchers can withdraw a family from this study if they consider that the family can no longer meet all the requirements of the study or if any of the procedures are considered possibly harmful for any of its members. Families participating in the study will be withdrawn if they meet any of the following criteria: (1) any circumstance that prevents them from performing the study procedures (i.e., using the educational materials or digital interactive tools and complying with the intake of the study products); (2) not attending study visits.

The losses and dropouts will be carefully recorded to ensure study reliability. The next participant who meets the eligibility criteria will replace the last participant who withdraws from the research until reaching the calculated sample size.

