### 2.10. Statistical Analysis

#### 2.10.1. Univariate Data Analysis

The data obtained from families in this study will be evaluated via an intention-to-treat (ITT) analysis, including data from families who drop out of the study, and per protocol (PP), that is, those families who have completed the treatment plan and who have exactly followed the instructions of the trial protocol. The error level of 0.05 will be set as a limit of statistical significance. A data analysis will be performed using the Statistical Software for Data Science (STATA, College Station, TX, USA) version 17.0 [63].

Mean and standard deviation will be reported for normally distributed variables and quantiles (25th percentile, median, and 75th percentile) for non-normally distributed variables. The Kolmogorov–Smirnov test and the Shapiro–Wilk test will be used to test for the normality of variables. The resulting scores of adherence to the MD (measured from the MEDAS and KIDMED questionnaires) will be used to calculate the mean differences between each intervention group and the control group before (V1) and after interventions (V2). Multiple comparisons (V2 vs. V0 and V2 vs. V1) of mean differences before and after interventions will be undertaken to assess the independent effect of interventions. The normality of the differences will be checked and, depending on the results, the following contrasts will be performed: parametric statistics (three-factor ANOVA with post hoc tests using the Bonferroni correction and considering the interactions between the following factors: app, educational materials, and snack products) will be used for normally distributed variables to compare differences in means and nonparametric statistics (Kruskal–Wallis test) will be used for non-normally distributed variables. Lineal regression and Spearman’s method will be used to test for correlations between normal and non-normal outcome variables, respectively.

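### Withdrawing randomised families who cannot use the components, without a planned V2 assessment, and replacing them conflicts with the stated intention-to-treat analysis and provides for drop-out twice

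*Protocol article*

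**What the plan says.** Section 2.6 of the protocol article randomises families after V0, and section 2.1 places the intervention in months 10 to 13. Section 2.6 also says that neither families nor research staff can be blinded.

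Section 2.8 states: "Families participating in the study will be withdrawn if they meet any of the following criteria". The two criteria are (1) being prevented from carrying out the study procedures, spelled out as using the educational materials or digital tools and taking the snacks, and (2) missing study visits. Losses are to be recorded, and then: "The next participant who meets the eligibility criteria will replace the last participant who withdraws from the research until reaching the calculated sample size".

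Section 2.7 has already allowed for loss: "assuming a 25% drop-out rate, the minimum group size is equal to 60 families per study group", up from 45.

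Section 2.10.1 promises an intention-to-treat analysis "including data from families who drop out of the study", alongside a separate per-protocol analysis. The main comparison is a three-factor ANOVA of before-after differences in MEDAS and KIDMED, with a rank-based alternative.

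**The concern.** Three features of the plan pull against each other.

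- **Withdrawal.** Section 2.8 takes families out of the study, and so out of follow-up, for a reason tied to the assigned components. Control families receive only basic guidelines (section 2.1), so the first criterion as worded does not reach them.
- **Replacement.** It takes place after randomisation, among staff who know the groups, and no allocation rule for the incoming family is given.
- **Analysis.** A family without a V2 score cannot contribute a before-after difference, so the intention-to-treat set risks becoming close to the per-protocol set.

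At stake is the comparability of the groups on the primary outcome. In a full-factorial design each component is present in four of the eight groups and absent from four. Removal that depends on having a component is therefore removal that depends on the factor being estimated. No later analysis can recover V2 scores that were never collected.

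**Working it through.** **1. The plan's sample size.** Inputs from section 2.7: "It was assumed that the alpha value would be equal to 0.05 and beta 0.20"; "The sample size was estimated using the analysis of variance (differences between 8 study groups" (the eight-group comparison); "with a common standard deviation equal to 1.19"; and the aim to "detect a minimum increase of 1 point". Sidedness is not stated; two-sided is assumed.

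With n = 2(z₁₋α/₂ + z₁₋β)²σ²/δ² and Bonferroni over all 28 pairs of eight groups (α = 0.05/28), n = 45 per group, with power 80.6%. The article does not say that this route was used. An unadjusted two-group comparison with the SD multiplied by √2 also gives 45. The 45 is not in dispute here.

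**2. The drop-out allowance.** n/(1 − d) with d = 0.25:
- per group: 45/0.75 = 60
- per country and group: 15/0.75 = 20
- in total: 360/0.75 = 480

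All match the article. In reverse, 480 × 0.75 = 360. At the assumed loss the requirement is met with no replacement.

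**3. What replacement adds.** Section 2.8 stops replacing at the calculated sample size, which could mean either total in section 2.7.

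| Reading | Replacements at 25% loss | Families enrolled |
|---|---|---|
| 480 completers | 0.25 × 480 = 120 in the first round; 640 − 480 = 160 in all | 480/0.75 = 640 |
| 360 completers | 360 − 480 × 0.75 = 0 | 480 |

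Only the first reading counts the 25% twice. Under the second, replacement acts only once loss passes 25%.

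**4. Who can be withdrawn.**

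| Criterion in section 2.8 | Control | Intervention groups |
|---|---|---|
| Prevented from using materials, tools or snacks | no such task | one to three components, by group |
| Missed visits | applies | applies |

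**5. Against the analysis.** Section 2.10.1 keeps drop-outs in the intention-to-treat set. Section 2.8 foresees recording losses but no further assessment of withdrawn families. The one missing-data method named, full-information maximum likelihood in section 2.10.2, is given for the structural equation model and not for the ANOVA.

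**6. Possible size of bias (illustration only).** Let a share p of an intervention group be removed, with those families benefiting r times as much as those kept. Assume no control removals and otherwise comparable groups. The effect in kept families, relative to the effect in all randomised, is 1/(1 − p + pr).
- p = 0.15, r = 0: 1/0.85 = 1.18
- p = 0.25, r = 0: 1/0.75 = 1.33
- any p, r = 1: 1.00

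Neither p nor r can be taken from the article, so these figures only show a range.

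**The case against.** A reader might go further than the text allows at four places.

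- **Randomisation is broken.** Section 2.8 does not say how a replacement is allocated. Section 2.6 has an outside researcher generate the list, and nothing rules out giving a replacement the next number on it. Non-random allocation follows only if the family takes the vacated place. What stands is that the rule operates after randomisation with unblinded staff and is silent on allocation.
- **Drop-out is counted twice, and 120 places are refilled.** Both hold only if the target is 480. At 360 the number refilled at 25% loss is zero. What stands is that there are two provisions for one loss and that the target is ambiguous.
- **Poor users are removed, with no counterpart in control.** The first criterion concerns being prevented from taking part, not low use, and low users who stay remain in the intention-to-treat set. Missed visits apply to control families too. What stands is that the first criterion is defined by tasks the control group lacks.
- **Effects are biased upward by 18%.** That rests on assumed inputs. A replacement joining late would have shorter exposure, which would dilute an effect. One joining between V0 and V1, where the Discussion expects high loss, could still have all three visits and the full three months.

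It is also fair to say that missing V2 scores are usually handled in a statistical analysis plan, and that section 2.8 does not forbid follow-up of withdrawn families. But section 2.8 states a rule of withdrawal from the study. If it is applied as written and no V2 score is sought, an analysis plan cannot restore the data.

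**Conclusion.** The point holds in this form: post-randomisation withdrawal under section 2.8, partly dependent on the arm and with no V2 assessment foreseen, would move the primary analysis towards completers and conflicts with the intention-to-treat analysis in section 2.10.1. Replacement after randomisation adds a risk of non-random allocation and is unnecessary at the assumed loss, because 480 × 0.75 = 360.

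The numerical cost of replacement runs from none (target 360, loss up to 25%) to 160 extra families (target 480, loss 25%). Upward bias is plausible if removed families would have benefited less, but neither its direction nor its size is established. The conclusion assumes that withdrawal from the study ends data collection, which is the natural reading and is not contradicted elsewhere. It should be settled before families are withdrawn or replaced, since it cannot be repaired afterwards.

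**What to change.** 1. Allow replacement only before randomisation. Keep the inflation to 60 per group as the sole allowance for later loss.
2. Separate stopping a component from leaving follow-up. Seek V2 MEDAS and KIDMED from every randomised family, online or by phone if a visit is missed, except those who withdraw consent to data collection.
3. Analyse every randomised family in its allocated group using all available scores, for example with a likelihood-based mixed model, and add a sensitivity analysis for data missing not at random. Keep the per-protocol analysis as secondary.
4. Reconcile sections 2.6, 2.7, 2.8 and 2.10.1, and state which total the calculated sample size means.

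The safety-related discontinuation rules in section 2.8 are not at issue here.

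The cost is protocol wording and some remote follow-up at V2. If loss exceeds 25%, the final number falls below 360 with no top-up.

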### 2.9. Data Management

All data will be collected and evaluated by experienced researchers and registered by the same researchers or study participants through predesigned forms in the Microsoft Forms web-based application.

The online forms will be self-completed by families at home in V0 and at the research center or school facilities in V1 and V2 with the assistance of the research staff. The forms will be adapted from validated scales for adults, adolescents, and children, and translated into the language of each country (Spanish, Turkish, French, and Arabic). They will comprise nine blocks of questions assessing various factors of interest (attitudes, intentions, self-efficacy, time allocation, work and household stress, health, nutrition, etc.), all of them integrated using a theoretical framework matrix [46,55,62] (Table 3).

Each family will be provided access to the Microsoft Forms links with a unique code previously assigned. Each member of the family must complete their own forms, except for children under 8 years of age, who will need the help of their parents for completion. In total, parents must complete 3 forms, adolescents 2 forms, and children under 12 years of age only 1 form. The average time for parents to complete the forms is 40 min, while it will only take about 20 min for adolescents and children under 12 years.

Anthropometric measurements will be collected at V1 and V2 by trained nutritionists with specific devices and registered in an online data collection notebook available for each family member in the Microsoft Forms web-based application.

Data on consumption patterns will be recorded in writing format in a notebook including a 7DWR. For one week, families must record all the foods and drinks and the amount consumed for each member of the family. In addition, they will have to record food expenses and keep shopping receipts. The researchers will check the data provided and transfer them to a common Excel database for the three enrolled countries to assess the economic and environmental impact.

Data generated with Microsoft Forms will be exported to Microsoft Excel. Access to the database will be restricted only to authorized personnel of the research team. All participant data will be hosted by the responsible researcher in protected folders in the cloud of the institutional Microsoft OneDrive server located in the European Economic Area to guarantee privacy.

### 2.10. Statistical Analysis

#### 2.10.1. Univariate Data Analysis

The data obtained from families in this study will be evaluated via an intention-to-treat (ITT) analysis, including data from families who drop out of the study, and per protocol (PP), that is, those families who have completed the treatment plan and who have exactly followed the instructions of the trial protocol. The error level of 0.05 will be set as a limit of statistical significance. A data analysis will be performed using the Statistical Software for Data Science (STATA, College Station, TX, USA) version 17.0 [63].

Mean and standard deviation will be reported for normally distributed variables and quantiles (25th percentile, median, and 75th percentile) for non-normally distributed variables. The Kolmogorov–Smirnov test and the Shapiro–Wilk test will be used to test for the normality of variables. The resulting scores of adherence to the MD (measured from the MEDAS and KIDMED questionnaires) will be used to calculate the mean differences between each intervention group and the control group before (V1) and after interventions (V2). Multiple comparisons (V2 vs. V0 and V2 vs. V1) of mean differences before and after interventions will be undertaken to assess the independent effect of interventions. The normality of the differences will be checked and, depending on the results, the following contrasts will be performed: parametric statistics (three-factor ANOVA with post hoc tests using the Bonferroni correction and considering the interactions between the following factors: app, educational materials, and snack products) will be used for normally distributed variables to compare differences in means and nonparametric statistics (Kruskal–Wallis test) will be used for non-normally distributed variables. Lineal regression and Spearman’s method will be used to test for correlations between normal and non-normal outcome variables, respectively.

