#### 2.10.2. Multivariate Data Analysis

Structural equation modeling (SEM) is a multivariate, hypothesis-driven technique that is based on a structural model representing a hypothesis about the causal relations among several variables. It will integrate the multiple factors affecting the adherence to the MD, including economic factors, social factors, psychological factors, quality of life, attitudes and beliefs related to food, health and healthy lifestyle, dietary habits, nutritional knowledge, and physical activity. It will test the direct and indirect effects of these multiple factors on the adherence to the MD. Fit indices like the root mean square error of approximation (RMSEA), the Tucker–Lewis index (TLI), and the comparative fit index (CFI) will be used to check for the adequacy of the fit of the model.

We will monitor model fit indices (RMSEA, TLI, and CFI) to ensure they fall within acceptable ranges and adjust the SEM model structure as necessary based on theoretical and statistical considerations to maintain interpretability. Missing data will be handled using Full Information Maximum Likelihood (FIML) estimation, an approach suited to SEM that reduces bias by using all available data without directly imputing values. Additionally, we will evaluate patterns of missingness to determine if data are missing at random (MAR) or missing not at random (MNAR) and will justify our handling approach accordingly. The reliability will be checked using three criteria, including the internal consistency, composed reliability, and average variance extracted (AVE). Cronbach’s alpha coefficient will be used to test the internal consistency of the scales. For validity, two criteria will be tested, including the convergent validity and the discriminant validity [62].

To address the socioeconomic and cultural differences among participants from Spain, Turkey, and Morocco, a stratified analysis will be conducted to examine the impact of socioeconomic and cultural contexts on participants’ responses to the interventions. By categorizing participants based on key demographic variables such as income, education level, and cultural background, we can gain insights into how these factors influence dietary behaviors and adherence to the MD.

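### The intention-to-treat analysis is said to include drop-outs, but the primary tests as written use only families with a V2 score, so the result under that label may be biased in either direction

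*Protocol article*

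**What the plan says.** Section 2.10.1 defines two analyses. The first is "evaluated via an intention-to-treat (ITT) analysis, including data from families who drop out of the study". The second is per protocol, limited to families who completed the plan and followed the instructions exactly.

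The same section fixes the outcome variable and the tests: "Multiple comparisons (V2 vs. V0 and V2 vs. V1) of mean differences before and after interventions will be undertaken to assess the independent effect of" the interventions. The changes in MEDAS and KIDMED go into a three-factor ANOVA (app, educational materials, snacks, with interactions and Bonferroni post hoc tests), or into a Kruskal–Wallis test if they are not normally distributed.

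Three other places bear on this:

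- Section 2.7 derives 45 families per group and then states: "However, assuming a 25% drop-out rate, the minimum group size is equal to 60 families per study group (20 families per country".
- Section 2.8 withdraws families who do not attend visits or cannot carry out the procedures. It replaces those who withdraw until the calculated sample size is reached.
- Section 2.10.2, on the structural equation model, holds the article's only missing-data method: "Missing data will be handled using Full Information Maximum Likelihood (FIML) estimation, an approach suited to SEM".

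**The concern.** The stated analysis set and the stated tests do not fit together. The set includes families who drop out. The tests work on a change that ends at V2, which a family lost before V2 does not have. If an analyst follows Section 2.10.1 literally, those families disappear from the analysis and the completer result is reported as intention-to-treat.

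That matters because the two results answer different questions: the effect of being assigned a component, and the difference among families who stayed to V2. The Discussion plans to propose the most effective components for national and regional health programmes, where the effect of assignment is the relevant one.

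The article expects loss. It plans for 25%, and the Discussion warns that the interval between V0 and V1 may cause high drop-out. Randomisation takes place after V0 (Sections 2.4 and 2.6), so families lost in that interval are already randomised.

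**Working it through.** **Inputs from the document.** Section 2.7: "It was assumed that the alpha value would be equal to 0.05 and beta 0.20"; "with a common standard deviation equal to 1.19"; a difference of 1 MEDAS point between intervention and control; 45 families per group, raised to 60 for 25% drop-out. Section 2.6: eight equal groups.

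**1. The plan's own figures.** The article does not state the multiplicity behind 45. A two-sided comparison of two means, with Bonferroni over all 28 pairs of eight groups, reproduces it:

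n = 2 × (z₁ + z₂)² × SD² / Δ² = 2 × (3.124 + 0.842)² × 1.19² / 1² ≈ 44.6, rounded up to 45.

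The allowance also reproduces: 45 / (1 − 0.25) = 60. In total, 60 × 8 = 480 are randomised and 45 × 8 = 360 retained, so 120 are expected to be lost. Both steps are sound. They show how many families are planned to have no V2 score.

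**2. Who enters the tests as written**

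| Scores available | In the stated ITT set | Has V2 − V1 | Has V2 − V0 |
|---|---|---|---|
| V0, V1, V2 | yes | yes | yes |
| V0, V1, V2, instructions not followed exactly | yes (not per protocol) | yes | yes |
| V0 and V1 only | yes | no | no |
| V0 only (lost before V1) | yes | no | no |

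The last two rows are the families that the ITT sentence promises to include. The second row shows that ITT and per protocol still differ as written.

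**3. Possible size of the bias.** The article gives no outcomes for drop-outs, so this step is an assumption with a range. Let the effect among completers be 1.0 point, drop-out d = 0.25 in every group, and r the share of that effect which drop-outs obtain.

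Effect in all randomised families = (1 − d) × 1.0 + d × r = 0.75 + 0.25r

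| r | All-randomised effect | Completer result of 1.0 is |
|---|---|---|
| 0 (change as controls) | 0.75 | 33% too high (1.0/0.75) |
| 0.5 | 0.875 | 14% too high |
| 1 | 1.00 | unbiased |
| 1.25 | 1.06 | 6% too low |

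More generally, suppose drop-outs change by a points less than completers in the intervention group and c points less in control. The all-randomised effect is then 1 − 0.25a + 0.25c. For a and c between 0 and 1 this runs from 0.75 (a = 1, c = 0) to 1.25 (a = 0, c = 1).

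**4. What a likelihood-based model can and cannot repair.** Two cases differ.

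- *Loss depends on an observed score.* Suppose 25% of one group is lost with a probability that depends on the baseline score, the true effect is 1.0, and baseline and final scores correlate at ρ. The completer contrast of changes is shifted by (1 − ρ)s, where s is the resulting imbalance in baseline means among retained families. In simulation with ρ from 0.3 to 0.8, the completer contrast gave 0.74 to 0.93 and the likelihood model 1.0. Those results imply s ≈ 0.26/0.7 = 0.37 and 0.07/0.2 = 0.35. If the dependence on baseline is reversed, the sign reverses.
- *Loss follows non-use, and drop-outs gain nothing (r = 0).* The mixed model returns 1.0, the same as the completer ANOVA, although the all-randomised effect is 0.75. Only an analysis that assigns drop-outs a control-like change addresses this case.

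**The case against.** **The analysis plan may supply the missing rule.** ANOVA can be run on imputed data, and a full protocol or SAP that is not shown may say how. This stands as a limit: a missing imputation method alone would be no finding, and it cannot be said that the ANOVA could only ever use completers. What remains is that Section 2.10.1 pairs a set that includes drop-outs with tests that exclude them as written, Section 2.8 removes and replaces families, and missing data are addressed only for another model.

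**A reader might infer that the effect is necessarily overstated.** The documents do not support that. They give no drop-out rates or outcomes by group, and step 3 gives bias in both directions or none. The Discussion's remarks on loss of adherence do not settle it either: a poorly adherent family that attends V2 has a score and stays in. What the Discussion says about drop-out itself concerns the interval before V1, when no component has been delivered.

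**A reader might also criticise the sample size.** Sizing on retained families and dividing by 0.75 is standard and correct here. Nor can one power figure be given for the ITT effect, because it depends on a basis that the article does not state. For a 0.75-point effect, power is roughly 0.6 with 28 Bonferroni pairs and over 99% for a factorial main effect that pools 240 against 240 families.

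**The 360 of 480 ignores replacement.** This is fair. Replacement changes the count in a way the article does not define, which is a further reason to reconcile Sections 2.8 and 2.10.1.

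**Conclusion.** The point holds as a conflict between a stated analysis set and a stated method. As Section 2.10.1 is written, the result called ITT covers only families with a V2 score: about 360 of 480 at the planned 25% drop-out if nobody is replaced. It may be too high, unbiased or too low. For a completer effect of 1.0 point, the all-randomised effect is 0.75 if drop-outs change as controls do, 1.0 if they keep the full effect, and up to 1.25 in the scenarios examined. These figures rest on equal drop-out across groups and on assumed outcomes for drop-outs. The full-information method of Section 2.10.2 should not be read as covering the primary tests, since it is stated for the structural equation model. The change should be made, and it is cheap.

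**What to change.** 1. **Section 2.10.1, ITT set.** Analyse all available MEDAS and KIDMED scores of every randomised family with a likelihood-based mixed model containing visit, app, education, snack and their interactions with visit. State its limit: it removes bias from loss that depends on observed scores, but not from loss that follows non-use.
2. **One prespecified sensitivity analysis.** Impute missing V2 scores by reference-based multiple imputation using the control group's change. For families lost before V1, use V0 as baseline where a V0 score exists. Section 2.4 lists the questionnaires at V1 and V2, while the eligibility limit in Section 2.2 and the V2-to-V0 comparison imply a V0 score, so the text should say whether one is recorded. Report the ITT conclusion together with this analysis.
3. **Labels and counts.** Call the ANOVA on families with both scores a completer analysis. Reconcile Sections 2.8 and 2.10.1 on how withdrawn and replacement families are counted in the ITT set.

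The cost is some rewording, one standard model and one imputation run. No families or measurements are added, and Section 2.7 needs no change on this account. The downside is slightly more analysis work and possibly a smaller ITT estimate.
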